### Outcomes

The primary outcome is OS (by months) of the patients within 18 months postoperatively. OS is the duration from the day of surgery to the date of death or last follow-up. The assessment of outcomes will be performed by trained research assessors who are blinded to the group allocation. They will assess the OS through telephone interviews with patients or their relatives every 3 months postoperatively.

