### Data collection and management

After obtaining informed consent, an independent research assistant will initiate baseline information collection one day before surgery. All personal information will be kept strictly confidential for research purposes only. Basic demographic information, including gender, age, vital signs, body mass index, past medical history, family history, smoking and drinking history, allergy history, operation history or anesthesia history, medication history, age-adjusted Charlson comorbidity index (aCCI, a widely used scoring system to predict outcomes of variety of medical conditions and malignancies, including the age of the patient as a correction variable of the final score of the CCI with the addition of one point for every decade over 40 years), ASA classification, KPS, Glasgow coma scale (GCS) will be collected. Functional classification of tumor (indicating the resectability of tumor) will be evaluated according to the results of preoperative MRI (Supplementary Table 4) [31, 32].

Intraoperative viable include vital sign parameters during anesthesia, total dose or infusion rate of anesthetic agents or other drugs during operation, such as inotropic or vasoactive drugs, mannitol, estimated blood loss, urine volume, the type, and dose of fluid and blood transfusion, duration of surgery and anesthesia. The usage of the analgesia pump (dosage, number of compressions, and effective compressions) will be recorded.

Postoperative medication will be recorded including sedative, analgesia, glucocorticoids, mannitol, and fluid infusion on 1 to 3 days postoperatively. The extent of resection (EOR) will be evaluated by a professional neuro-radiologist according to the results of the MRI within 72 h postoperatively (Supplementary Table 4).

The median follow-up time will be 18 months postoperatively before the study was terminated. The patients and their legal representatives will be told to be followed up by telephone at 3, 6, 9, 12, 15, and 18 months postoperatively. The start points of simultaneous radiotherapy and chemotherapy, patient compliance, adverse events or complications and treatment, the European organization for the research and treatment of cancer on quality of life (EORTCQLQ-C30), and the Karnofsky performance Status (KPS) Scale will be evaluated every 3 months postoperatively. Strict data management will be kept including double data entry and establishing range checks for data values.

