### Sample size calculation and statistical analysis

The sample size is estimated by using PASS 2011 software (NCCS LLC). We calculated the sample size based on the primary outcome. A two-sided Log-rank test with an overall sample size of 344 subjects (172 in the intravenous group and 172 in the inhalation group) achieves 80% power at a 0.05 significance level to detect a hazard ratio of 1.66 when the overall survival is 15 vs. 11 months in intravenous and inhalation group, respectively. The study will last for about 42 months, of which subject accrual (entry) occurs in the first 24 months with the proportion dropping out of the two groups being 0.1, respectively.

Analysis will be conducted using SPSS software (version 23.0). The Kolmogorov-Smirnov test will be used to test data normality. Normally distributed continuous variables will be described as the means with standard deviation (SD) and compared by using independent *t* tests. Non-normally distributed variables will be summarized as medians and interquartile range (IQR) and compared by using Mann-Whitney *U* tests. Categorical variables will be described as numbers (*n*) and percentage (%) and compared using chi-square or Fisher’s exact tests.

The Kaplan-Meier method will be used to describe the time-to-event data (OS and PFS), and the log-rank test will be used for comparisons. Univariate and multivariate Cox proportional hazard regressions will be used for survival analysis. Together with the anesthesia type, variables with *P*<0.1 in the univariate analysis will be regarded as candidate variables for the multivariable model. A significance level of *P*<0.05 will be used to indicate statistical significance. The imputation method will be used for dealing with missing data. The impact of missing data will be estimated by sensitivity analysis. Additionally, subgroup analysis will be undertaken to assess the association between anesthesia and the outcome according to the aCCI, KPS, EOR, WHO grade, duration of anesthesia, and whether using chemotherapy or not. No interim analysis will be done and the trial will not early terminate.

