The patients receiving reoperation for postoperative complications with different anesthesia methods will be analyzed with the intention-to-treat principle, a secondary per-protocol analysis where patients with protocol deviations are removed. The patients whose postoperative pathological results excluded high-grade glioma will be analyzed with the per-protocol principle. The patients of dropouts, lost follow-up, or end of the study will be treated as censoring in survival analysis.

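### The plan censors dropouts for overall survival and nowhere provides for keeping and using their vital status, although a relative's report would do; securing it is a cheap improvement

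*Protocol article*

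**What the plan says.** The last sentence on the analysis, in the protocol article's section on sample size and statistical analysis, is "The patients of dropouts, lost follow-up, or end of the study will be treated as censoring in survival analysis". It names three groups, and dropouts are distinct from patients lost to follow-up. The term dropout is not defined.

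Under Outcomes, the endpoint is stated as "The primary outcome is OS (by months) of the patients within 18 months postoperatively", with "OS is the duration from the day of surgery to the date of death or last follow-up". Deaths are found by telephone: "They will assess the OS through telephone interviews with patients or their relatives every 3 months postoperatively". Data collection and management says that patients and their legal representatives will be "told to be followed up by telephone at 3, 6, 9, 12, 15, and 18 months postoperatively". The same three-monthly assessments cover "patient compliance, adverse events or complications and treatment, the European organization for the research and treatment of cancer on quality of life" and performance status.

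The sample size section assumes "the proportion dropping out of the two groups being 0.1, respectively", without a time unit. It also promises imputation and a sensitivity analysis for missing data, without saying whether either applies to censored survival times. Under Intervention, the randomised anaesthetic is stopped at the end of surgery.

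**The concern.** In a trial of continuing treatment, dropout can mean stopping the drug. Here the treatment is over on the day of surgery, so a later dropout can only be stopping participation. A family that no longer wants questionnaires or scans may still be able to say whether the patient is alive and, if not, when death occurred. The protocol already accepts that source. A rule that censors all dropouts therefore gives up deaths on the primary endpoint that could be obtained.

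Two things are at stake. One is precision, because fewer deaths mean less power. The other is validity. Kaplan-Meier, log-rank and Cox analyses assume that a censored patient has the same outlook as those still followed. With entry restricted to KPS below 80 and planned survival of 15 and 11 months, it is plausible that some patients leave because they are declining. Survival would then be overstated and, if dropout also differed between arms, the treatment comparison would be biased.

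**Working it through.** **Inputs.** From the protocol: 172 patients per arm, survival of 15 months (propofol) and 11 months (sevoflurane), an 18-month horizon, and dropout of 0.1 per arm. Assumed here: exponential survival with 15 and 11 as medians, and 0.1 as the proportion over 18 months.

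**The plan's own figure.** The plan states "A two-sided Log-rank test with an overall sample size of 344 subjects", with 80% power at a hazard ratio of 1.66. Schoenfeld's formula gives 4 × (1.960 + 0.842)² / (ln 1.66)² = 122.2, so 123 deaths. A total of 344 follows only if the propofol median is 15, the sevoflurane median is 15/1.66 = 9.04 rather than 11, and dropout is 0.1 *per month*. The probability of an observed death is then 0.359, and 123/0.359 = 343; a Lakatos-type calculation gives 344.4. So the unit of 0.1 matters, and both readings are carried below.

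**Deaths with complete vital status.** The probability of death by 18 months is 1 − 2^(−18/median).
- Propofol: 0.565 × 172 = 97.1
- Sevoflurane: 0.678 × 172 = 116.7
- Total: 213.8

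**Case A: 10% dropout unrelated to prognosis, censored.** With λ = ln 2/median and η = −ln(0.9)/18 = 0.00585, deaths per arm are 172 × λ/(λ+η) × [1 − e^(−18(λ+η))].
- Propofol 92.9, sevoflurane 111.8, total 204.7
- Loss: 213.8 − 204.7 = 9.1 deaths (4%); for 5% to 20% dropout, 4.5 to 19 deaths
- Power, Φ(ln HR × √D / 2 − 1.96): 0.602 against 0.621 at a hazard ratio of 15/11 = 1.36, and 0.952 against 0.960 at 1.66
- Bias in the hazard ratio: none

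**Case B: every dropout would die within 18 months and leaves 0 to 3 months before death (pessimistic bound, large-sample simulation, 10% per arm).**
- Deaths 79.9 + 99.4 = 179.3, a loss of 34.5, which is in effect 0.1 × 344 by construction
- Kaplan-Meier survival at 18 months: about 50% and 38%, against 43% and 32%
- Propofol/sevoflurane hazard ratio: about 0.71, against 11/15 = 0.73

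**Case C: no true effect (13 months in both arms), mechanism as in B.** Hazard ratios are propofol/sevoflurane.

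| Dropout, propofol / sevoflurane | Hazard ratio |
|---|---|
| 10% / 10% | 1.00 |
| 8% / 12% | about 1.08 |
| 5% / 15% | about 1.20 |

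More dropout in the sevoflurane arm thus biases against propofol; with the arms exchanged, 1/1.20 = 0.83.

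**Case D: milder mechanism.** The hazard of death after dropout is multiplied by k. Hazard ratios are sevoflurane/propofol, the plan's orientation, with a true value of 1.36 before dropout.
- 10% in both arms, k = 1 to 4: 1.36 to 1.37 censored, 1.36 with full follow-up
- 5% propofol / 15% sevoflurane, k = 2 to 4: 1.37 censored, 1.41 to 1.44 full
- 15% / 5%, k = 2 to 4: 1.36 censored, 1.27 to 1.32 full

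**If 0.1 is per month.** Absent death, 1 − 0.9^18 = 85% would have dropped out by month 18. Over the 42-month design at 15 and 11 months, deaths would be about 115 instead of 270.

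**The case against.** The strongest answer is that the sentence concerns analysis, not data collection. A reader might infer from it that calls stop at dropout and that these patients are censored instead of being followed. The protocol does not say so. It schedules calls to patients, representatives or relatives through month 18, and is silent on whether they continue after dropout. Dropout may also mean withdrawal of consent to any further data, where censoring is the only option. Censoring unreachable patients and those at the end of the study is standard. Withdrawal procedures may sit in the full protocol, which is not shown.

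A reader might also infer that the censoring is known to be informative, or that a loss of about 34 deaths is to be expected. Neither is supported. No reasons for dropout are given, relatives can answer for a declining patient, and the larger loss follows from assuming that every dropout dies within 18 months. The plan assumes the same dropout in both arms, and patients and assessors are blinded, so 5% against 15% is an illustration only.

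All this stands, but it does not remove the point. If calls do continue and a death is reported after dropout, the Outcomes definition would count it while the analysis rule would censor the patient. The text needs repair either way. The promised sensitivity analysis cannot supply dates of death that were not collected.

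**Conclusion.** The point holds as a cheap improvement, not as a demonstrated bias. The stated rule censors a group that may still be reachable, for an endpoint that one question to a relative can settle, and nothing in the protocol keeps those deaths in the primary analysis.

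At 10% dropout overall, the cost ranges from slight (Case A) to the pessimistic bound (Case B). Even that bound gives no spurious effect when dropout is equal; a false effect needs dropout that is both related to prognosis and unequal between arms. These sizes rest on exponential survival, an 18-month cap and 0.1 read as an overall proportion. The loss of deaths would be much larger if 0.1 were a monthly rate.

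**What to change.** Replace the censoring sentence with a rule that separates two groups: patients who stop calls, questionnaires or MRI, and patients who refuse any further data.

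- For the first group, continue asking the patient or a relative for vital status and date of death to month 18, and count those deaths in the overall survival analysis.
- Censor overall survival at the last date known alive only for refusal of further data, for patients who cannot be reached, and at month 18.
- State the time unit of the 0.1 dropout assumption.

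The cost is a changed sentence, a line in the consent form and a few short calls by the existing follow-up staff, for about 34 patients at 10% dropout (0.1 × 344). Some families will decline, so a few patients will still be censored early.

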### Reporting of adverse events

Data monitoring committee will not be set up in the trial for the sample size is not very large. However, an auditing trial will be conducted twice per year and the process will be independent from investigators and the sponsor. All adverse events (AEs) will be closely monitored until a stable situation has been reached. The chief investigator will be informed of any serious AEs and determine the severity and causality of these events. All AEs associated with this study will be recorded and reported to the Ethics Committee as part of the annual report. The chief investigator will be responsible for collecting the details about the causes of AEs, treatment, prognosis, and reporting SAE to the Ethics Committee immediately. The incidence of adverse effects will be described as percentages and frequencies for each group. Chi-square and Fisher’s exact test will be used for comparison between groups. The researcher will have access to the final trial data set.

### Protocol amendment

The chief investigator will be responsible for any decision to amend the protocol. If there is any modification (e.g., changes to eligibility criteria, outcomes, or analysis), the principle investigator will report and gain approval from the China Ethics Committee of Registering Clinical Trials prior to implementation, by communicating with relevant other members (e.g., investigators, participants, registries, journals, and regulators).

## Discussion

This is a randomized controlled trial to compare the effect of intravenous or inhalation anesthesia maintenance on the OS in supratentorial HGG patients of KPS<80. There are some well-known risk factors such as age at diagnosis, KPS, histological type, distant metastasis, and extent of surgical resection for predicting the OS of patients with HG G [31].

Intravenous and inhalation anesthesias are the common anesthesia methods for HGG resection. But they are different in some aspects. Firstly, intravenous anesthesia inhibits the invasion of the tumor cells and host stress response and protects cellular immunity, while inhalation anesthesia has the opposite effect. Secondly, during craniotomy, the mass effect of the tumor and the peritumoral edema always lead to severe intracranial hypertension and brain herniation. As nearly all inhalational agents increase the cerebral blood flow and ICP, propofol has the opposite effect to decrease the ICP and facilitate tumor exposure. Thirdly, intravenous anesthesia promotes postoperative rapid recovery of the patients. Postoperative pain, nausea and vomiting, and shivering appear less frequently with propofol-maintained anesthesia [16, 33, 34]. However, the hemodynamic stability, time to extubation, and early cognitive functions were similar with two anesthetic techniques [35].

In this RCT study, we will fully evaluate the patients before operation, including physical status, neurological function, and imaging results. During the operation, standard anesthesia management, anesthesia depth monitoring, and individualized medication according to the protocol will be conducted by specially trained personnel. After surgery, the patients will be followed up regularly by designated personnel for the recovery, adverse events, complications, treatment, PFS, and OS.

Although the intervention of our study is intravenous or inhalation anesthesia, inhalational anesthetics will not be used for induction, as it is not routine in clinical practice. So propofol induction will be used in both groups. We regard the effect of a single bolus of propofol as minimal and short, which will be eliminated completely before surgical incision.

We use the survival time to calculate the sample size. As the median OS was 15 vs.11 months in TIVA and inhalation group, with a hazard ratio of 1.66, the calculated sample size is 344, which is more credible in survival analysis.

Our study will optimize the ideal anesthesia regimen for patients undergoing brain tumor resections, not only from the point of view on perioperative anesthesia and analgesia, but also from the point of view on clinical outcomes of overall survival in HGG patients.

## Trial status

The trial was registered at ClinicalTrials.gov on 29 April 2016 (identifier NCT02756312) and the last update time of the trial is 9 Sep 2020. The study was approved by the Ethics Review Committee of China Registered Clinical Trials (Ethics Review No. ChiECRCT-20200049). The trial has not yet recruited any participants till now. The anticipated completion date will be in December 2022.

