### Study population

#### Participants

Patients undergoing elective tumor resection under general anesthesia will be recruited consecutively from neurosurgical wards in Beijing Tiantan Hospital, Capital Medical University from Sept 2020 to December 2023.

Inclusion criteria include age more than 18 and less than 80 years old, preoperative KPS less than 80, and diagnosis of HGG by preoperative magnetic radiology imaging (MRI). The patients or their legal representatives agree to provide for the collection and use of participant data and biological specimens and sign written informed consent.

Exclusion criteria include a history of other operations after diagnosis of HGG, patients with recurrence and metastasis of gliomas or with malignant tumors of other organs, emergency surgery, pregnant or breastfeeding women, allergic to study drugs, patients who need electrophysiological monitoring during operation will be removed.

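### Recruitment dates, accrual period and completion date cannot all hold, and the end of study at which patients are censored is not fixed

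*Protocol article*

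**What the plan says.** Three sections of the protocol article give dates or durations.

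- **Participants:** patients are recruited "from Sept 2020 to December 2023".
- **Sample size calculation and statistical analysis:** "The study will last for about 42 months, of which subject accrual (entry) occurs in the first 24 months".
- **Trial status:** "The trial has not yet recruited any participants till now. The anticipated completion date will be in December 2022". The same paragraph notes that "the last update time of the trial is 9 Sep 2020".

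Two further statements determine who has a full observation window. The statistical section says: "The patients of dropouts, lost follow-up, or end of the study will be treated as censoring in survival analysis". The Outcomes section sets the primary outcome as overall survival within 18 months of surgery. Data collection and management schedules telephone contacts every 3 months up to month 18, but describes follow-up before the study ends as a median of 18 months, not as a minimum for each patient.

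**The concern.** The completion date precedes the close of recruitment by 12 months, and a 40-month recruitment window does not fit 24 months of accrual. These are conflicts between current statements, whatever date each was written.

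Censoring at the end of a study is standard and harmless when that end is fixed so that everyone has been observed for the full horizon. Here the end can be read in several ways. A patient operated on late in recruitment may or may not have 18 months of observation, depending on which statement the trial team follows. Closing before the last patient reaches month 18 removes deaths from the primary log-rank comparison. A follow-up described by its median does not rule that out.

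**Working it through.** **1. Calendar.** Count September 2020 as month 1.

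| Statement | Arithmetic | Result |
|---|---|---|
| Recruitment to December 2023 | 4 + 12 + 12 + 12 | 40 months, not 24 |
| 24-month accrual | September 2020 + 24 | ends August 2022 |
| 42-month study | September 2020 + 42 | ends February 2024 |
| Completion December 2022 | 4 + 12 + 12 | month 28, 12 months before recruitment closes |
| Last patient (December 2023) reaches month 18 | 40 + 18 | month 58, June 2025 |

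The sample size section is coherent on its own: 24 + 18 = 42, so the last patient would have 18 months. It does not fit the other two sections.

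**2. Share of patients able to reach 18 months.** With uniform accrual over 40 months and closure at month 42, only those entered by month 42 − 18 = 24 have the full window: 24/40 = 60%. The other 40% have between 2 and 18 months.

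**3. Expected deaths.** From the plan: 344 patients, 172 per arm; medians 15 and 11 months; hazard ratio 1.66; 18-month horizon; dropout 0.1 per arm. Assumed, because the article does not say: exponential survival, uniform accrual, and the 10% loss spread evenly to month 18.

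- Hazards: λ = ln 2/median, so 0.04621 (median 15) and 0.06301 (median 11). Loss rate: δ = −ln(0.9)/18 = 0.00585. Write s = λ + δ.
- A patient with the full window dies under observation with probability (λ/s)(1 − e^(−18s)): 0.5399 and 0.6501.
- Averaged over windows of 2 to 18 months, the probability is (λ/s)[1 − (e^(−2s) − e^(−18s))/(16s)]: about 0.345 and 0.432.
- Full follow-up: 172 × (0.5399 + 0.6501) = 204.7 deaths.
- 40 months' accrual, closure at 42: 0.6 × 0.5399 + 0.4 × 0.345 = 0.4619 and 0.6 × 0.6501 + 0.4 × 0.432 = 0.5628, giving 172 × (0.4619 + 0.5628) = 176.2 deaths.
- Loss: 204.7 − 176.2 = 28.5 deaths, or 14%.

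Medians of 15 and 11 imply a hazard ratio of 15/11 = 1.364. A ratio of 1.66 with the 15-month median kept implies 15/1.66 = 9.04 months in the other arm; the same steps then give 216.5 and 187.5 deaths.

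**4. Power.** Schoenfeld, two-sided 0.05, 1:1: Φ(½ √d × ln HR − 1.96), where d is the number of deaths.

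| Accrual / closure (months) | Can reach 18 months | Deaths, power at 15 vs 11 | Deaths, power at 15 vs 9.04 |
|---|---|---|---|
| 24 / 42 | 100% | 204.7, 60% | 216.5, 96% |
| 40 / 42 | 60% | 176.2, 54% | 187.5, 93% |
| 40 / 58 | 100% | 204.7, 60% | 216.5, 96% |

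The first and third rows are identical. Once every patient has 18 months and the analysis stops there, the length of accrual does not change deaths or power. The loss comes only from closing early. The planned 80% is not reproduced in any row, because a hazard ratio of 1.66 does not match medians of 15 and 11. That is a separate matter.

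**The case against.** The best defence is that full follow-up is clearly intended. The primary outcome has an 18-month horizon, calls are scheduled to month 18, 24 + 18 = 42 gives the last patient 18 months, and the plan rules out interim analysis and early termination. On that reading the end of study censors nobody before month 18. This is a fair account of intent and it limits the severity. It does not remove the conflict: the 42-month figure protects the last patient only if accrual stops at 24 months, and the Participants section says otherwise. The full protocol may define the end of study, but nothing shown does.

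Three stronger readings are tempting, and the documents do not support them.

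- **That data will be locked in December 2022, with a collapse in power.** "The anticipated completion date will be in December 2022" is an anticipated date in a status note, not a data-lock rule. With 40-month accrual, only about 344 × 28/40 = 241 patients would be enrolled by then, so any power figure for that date mixes under-enrolment with censoring.
- **That a trial published in September 2022 with no patients cannot meet its dates.** "The trial has not yet recruited any participants till now" is undated. Beside a last update of 9 September 2020 it may describe the trial at its planned start.
- **That 40 months of accrual invalidates the power statement.** The table above shows that accrual length alone has no effect under full 18-month follow-up.

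**Conclusion.** The point holds as an inconsistency that should be fixed. The recruitment window, the accrual period and the completion date are incompatible, and the censoring rule refers to an end of study that the article does not pin down.

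The consequence is moderate. In the plausible bad case, recruiting to December 2023 and closing at 42 months, about 40% of patients cannot reach the primary horizon and about 28 of 205 expected deaths are lost. Power drops by 6 points at medians of 15 and 11, and by 3 points at a hazard ratio of 1.66, where it stays above the planned 80%. The calendar conflict itself needs no modelling; these sizes rest on the survival, accrual and loss assumptions listed in the working.

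A reader might attribute the gap between 60% and the stated 80% to the calendar. It is not due to the calendar: it remains when every patient has full follow-up.

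**What to change.** - Define the end of study, and the data lock for the primary analysis, as 18 months after the last patient's surgery.
- In Data collection and management, replace the median follow-up statement with a commitment to follow every patient to death or 18 months.
- Align Participants, the sample size section and Trial status to one calendar. If recruitment runs to December 2023, that means 40 months of accrual, about 58 months in total, and completion in about June 2025.

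The cost is wording in a few places and a later stated completion date. No new power calculation is needed because of accrual length.
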